## Abstract

**Background:**

With increasing obese populations worldwide, developing interventions to modulate food-related brain processes and functions is particularly important. Evidence suggests that transcranial direct current stimulation (tDCS) over the dorsolateral prefrontal cortex (DLPFC) may modulate the reward–control balance towards facilitation of cognitive control and possible suppression of reward-related mechanisms that drive food cue-induced craving. This protocol describes a clinical trial that investigates the neurocognitive mechanisms of action for tDCS to modulate food cue-reactivity and cravings in people with obesity.

**Method:**

The NeuroStim-Obesity trial is a prospective, randomized, sham-controlled, double-blind single-session tDCS trial targeting food craving in those with obesity or overweighed. Once randomized, 64 adults with obesity or overweighed complete one session in which they receive either active or sham tDCS over the DLPFC (anode F4 and cathode F3, 2 mA intensity for 20 min). The primary outcome is change in neural response to the food cue-reactivity task in the ventral striatum after a single-session bilateral tDCS compared to sham stimulation. Secondary outcomes include changes in food craving evaluated by the Food Craving Questionnaire-State (FCQ-S). We will also explore the predictive role of brain structure and functional networks assessed by structural and functional magnetic resonance imaging (MRI) during both task performance and the resting-state that are acquired pre- and post-intervention to predict response to tDCS.

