The therapeutic potential of tDCS intervention for obesity is hypothesized to be based on the modulation of dysregulated top–down control by prefrontal cortex (PFC) function and reward processing in subcortical-limbic structures, mainly the ventral striatum. In recent years, data derived from neuroimaging and cognitive assessments provide evidence that food cue-reactivity, particularly in obese persons, is associated with dysregulated activities within the prefrontal regions, specifically, the dorsolateral prefrontal cortex (DLPFC). The potential for DLPFC neuromodulation might remediate these dysregulated activities within prefrontal brain regions that have been associated with both impaired inhibitory control (i.e., binge eating and purging) and poor cognitive flexibility (e.g., the obsessive concerns with eating, weight, and shape) [12, 22–24].

Accordingly, therapeutic strategies that modulate brain activity in the DLPFC might regulate or suppress food cue-reactivity, cravings, and appetite. Examining the effect of cortical activity modulation using high-frequency rTMS over the left DLPFC in eating disorders and obesity was tested in many studies and a temporary anti-craving effect of this modulation has been demonstrated [27, 28]. Another clinical study also reported beneficial effects of using high-frequency rTMS applied over the left DLPFC to modify cue-induced food cravings and binge eating in people with a bulimic eating disorder [29]. This finding was replicated using bilateral tDCS to the DLPFC (anode over F4/cathode over F3), which demonstrate a reduction in self-reported cravings for active stimulation as compared to sham stimulation [30–32].

However, no study has evaluated the neurofunctional mechanisms of action of tDCS on food cue-reactivity. Therefore, the present study was designed as a randomized parallel-design, sham-controlled, double-blind trial to investigate the neurofunctional mechanisms of action for tDCS to modulate food cue-reactivity and cravings in ones with obesity or overweight problems using fMRI. We focused on the following aims in this trial:

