#### Primary outcomes

The primary outcome is the changes from pre-fMRI to post-fMRI in VAS scores (for food craving) at post-tDCS compared to changes at pre-tDCS in the sham and active tDCS groups.

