#### Secondary outcomes

Change in FCQ-S scores from before tDCS to after tDCS, as measured by Food Craving Questionnaire-State [40]Change in resting-state functional connectivity between cortical and subcortical regions, as assessed by correlation between spontaneous BOLD signal fluctuations in subcortical ROIs and voxels within the prefrontal cortex and insula from before tDCS to after tDCSChange in resting-state functional connectivity under the stimulated area, as assessed by correlation between spontaneous BOLD signal fluctuations in the cortical area under the anode/cathode electrodes and whole brain from before tDCS to after tDCSChange in task-based functional activation in the prefrontal cortical areas and subcortical-limbic areas, as assessed by the BOLD signal changes with voxel-wise analysis in the regions of interests (ROIs) (prefrontal cortex, insula, thalamus, ventral striatum, and extended amygdala) from before tDCS to after tDCSChange in task-based functional connectivity between the cortical and subcortical regions, as assessed by psychophysiological interaction (PPI) between spontaneous BOLD signal fluctuations in subcortical ROIs and voxels within the prefrontal cortex and insula from before tDCS to after tDCSChange in task-based functional connectivity under the stimulated area, as assessed by psychophysiological interaction (PPI) between spontaneous BOLD signal fluctuations in the cortical area under the anode/cathode electrodes and whole brain from before tDCS to after tDCSChange in Resource Allocation Index (RAI) in rs-fMRI, as assessed by correlation among default mode network (DMN), saliency network (SN), and executive control network (ECN) in rs-fMRI from before tDCS to after tDCS [41]

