### Sample size estimation

Based on a recent study in the field using single-session bilateral tDCS over the DLPFC compared to sham tDCS [31], we estimated an effect size of 0.55. To demonstrate the intervention effect in the primary outcome, 64 participants (32 per tDCS group) need to be included in the analysis with a two-group *t*-test with a 0.05 two-sided significance level and a power of 80%. Sample size estimation was conducted using PASS software [47].

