### Statistical methods

Baseline participant characteristics will be presented as mean ± standard deviation for continuous variables or percentages for categorical variables. Participant demographics data will be compared between the active tDCS and sham tDCS groups, using a two-sample *t*-test (Student’s *t*-test).

To control for the tDCS intervention efficacy, a repeated-measures analysis of variance (ANOVA) will be performed on FCQ-T with time (before/after tDCS) as the within-subject factor and group (active tDCS/sham tDCS) as the between-group factor. The same strategy will be followed for behavioral and neuropsychological data.

Changes in functional neural parameters (resting-state and task-related fMRI) will be preprocessed and analyzed using the Analysis of Functional NeuroImages (AFNI) [48]. To assess brain–behavior associations, the correlations between changes in brain activity/connectivity and subjective craving will be investigated using the Pearson correlation test. As an exploratory analysis, the definition of major prognostic factors for response to active tDCS will be assessed using the exploratory regularized regression model. Assessment of the model validity will be performed using leave-one-out cross-validation within this dataset and will be validated with subsequent test datasets in the future studies. All statistical analyses will be run using the R Statistical Package [49]. There will be no interim analysis. The investigators will be empowered to stop the trial under the following circumstances:
Harm
There is a significant increased risk for serious adverse events, including severe itching and redness at the electrode site, nausea, dizziness, or drowsiness.Safety
Significant safety concerns emerge and the Research Ethics Committee of Iran University of Medical Sciences choose to pause or stop the trial.

We do not plan to conduct additional analyses, both subgroup and adjusted analyses.

We expect very low missing data in our baseline neuropsychological covariates and in the food craving measures (Table 1). Missing data will be reported in the publication. More than 5% missing data will result in multiple imputation with the generation of 40–50 imputed data sets to be analyzed separately and then aggregated into one estimate of the effect of the intervention on the primary and secondary outcomes. Missing data will be supplemented by the Multivariate Imputation by Chained Equations (MICE) method [50, 51].

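### The abstract and the outcomes section name different primary outcomes, so the endpoint of the confirmatory test is not fixed

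*Protocol article*

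**What the plan says.** All references are to the Protocol article.

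- **Abstract, Method:** "The primary outcome is change in neural response to the food cue-reactivity task in the ventral striatum", active against sham. FCQ-S craving is secondary here, and VAS craving is not mentioned.
- **Primary outcomes:** "The primary outcome is the changes from pre-fMRI to post-fMRI in VAS scores (for food craving"), with the change after tDCS set against the change before it, by group. No other primary outcome is listed.
- **Secondary outcomes:** task activation is analysed voxel-wise in five regions ("prefrontal cortex, insula, thalamus, ventral striatum, and extended amygdala"). Ventral striatal activation is therefore secondary in this section.
- **Sample size estimation:** "we estimated an effect size of 0.55", taken from an earlier single-session bilateral tDCS study (reference 31), with a two-group t-test, "0.05 two-sided significance level and a power of 80"%, and 32 participants per group. The calculation is for the primary outcome, which is not named.
- **Statistical methods:** "a repeated-measures analysis of variance (ANOVA) will be performed on FCQ-T with time (before/after tDCS) as the within-subject factor" and group as the between-subject factor. Then: "The same strategy will be followed for behavioral and neuropsychological data". Imaging is assigned to AFNI. No analysis is labelled primary.
- **Background:** the group of studies that includes reference 31 is said to "demonstrate a reduction in self-reported cravings for active stimulation as compared to sham stimulation".

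**The concern.** One version of the primary outcome is a BOLD response in a single brain region. The other is a self-report score. They are different variables on different scales, and each is presented as the sole primary outcome. Nothing in the article says which governs.

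Two things are at stake. First, if the choice is still open when results are known, the outcome with the better result can be called primary, and the nominal 5% error rate no longer describes the headline test. Second, a power statement has meaning only for a named endpoint. Here the 80% claim is attached to an outcome that the reader cannot identify.

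**Working it through.** **Does any other section settle the endpoint?**

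- The first listed aim concerns subcortical-limbic reactivity to food cues, and the Background gives the trial a neurofunctional purpose. Both favour the abstract's version.
- The sample-size source is described as a self-reported craving study, which favours a craving endpoint. The article does not say which craving scale that study used. FCQ-S, which is secondary in both the abstract and the outcomes section, fits the description as well as VAS does.
- The Statistical methods section names FCQ-T, which is neither version of the primary outcome and is not a listed secondary outcome. If VAS craving falls under behavioral data, it inherits an ANOVA with two times, before and after tDCS. The VAS outcome uses four times (T1, T3, T5 and T7 in Table 1) and is a change of changes, (T7−T5)−(T3−T1). The two-level time factor does not directly describe that quantity.
- The sample-size section uses a two-group t-test, while the Statistical methods section uses a repeated-measures ANOVA.

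The sections point in different directions, and no pairing of one endpoint with one test is fixed.

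**Size of the error-rate risk.** Take two candidate outcomes, each tested at 0.05, with success claimed if either is significant. Under independence:

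1 − (1 − 0.05)² = 1 − 0.9025 = 0.0975, or 9.75%.

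Positive correlation between the outcomes lowers this figure.

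**Does the stated sample size identify or support an endpoint?** The inputs, from Sample size estimation, are effect size 0.55, two-sided alpha 0.05, power 80% and 32 per arm. The type of effect size is not stated. Reading it as Cohen's d is an assumption.

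- Per-arm size by normal approximation: 2 × ((1.960 + 0.842)/0.55)² = 51.9, so 52 per arm (104 in total). The t-test gives 52.9, so 53 per arm (106 in total). The plan states 32 per arm (64 in total), so its figure is not reproduced.
- Power at 32 per arm: the noncentrality is 0.55 × √(32/2) = 0.55 × 4 = 2.20. The normal approximation gives Φ(2.20 − 1.96) = 0.59, and the t-test gives 0.58. The plan states 0.80.
- Effect detectable with 80% power at 32 per arm: d = 0.71.
- Other readings do not give 64 either. A one-sided test needs 41 to 42 per arm. A paired or one-sample t-test needs 28 in all. Reading 0.55 as Cohen's f needs about 14 to 15 per arm.
- Reaching 32 per arm with 0.55 would need an unstated pre–post correlation. For ANCOVA it is √(1 − 32/51.9) = 0.62. For a change score it is 1 − 32/(2 × 51.9) = 0.69.

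The calculation therefore neither reveals which outcome it was made for nor delivers 80% power on the plain reading of its inputs.

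**The case against.** The contradiction itself is hard to defend. It is in current text, not in an amendment log. Condensing a protocol into an article can drop detail, but it does not turn one primary outcome into another. The good objections are to stronger conclusions that a reader might draw.

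- **That the confirmatory test is wholly undefined.** Test type, alpha and sidedness are stated in the sample-size section. It is the endpoint that is open.
- **That the type I error rate is 9.75%.** No section sets up an either/or success rule, and each names one primary outcome. The figure applies only if the choice is made afterwards and the outcomes are independent.
- **That FCQ-T is a third candidate, giving 1 − 0.95³ = 14.3%.** No section calls FCQ-T primary. Its appearance in the Statistical methods section is a mismatch to repair, not a third primary outcome.
- **That the voxel-wise, five-region analysis inflates the error further.** That form belongs to the secondary outcome. The abstract's primary outcome is a single region.
- **That the sample size supports VAS craving and only the BOLD version lacks support.** The article does not show that 0.55 came from a VAS, still less from this change of changes. With 0.55 read as d, 32 per arm falls short of 80% power for either endpoint.
- **That the registry entry disagrees with the article.** The record is not at hand, so this can only be checked.

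All of these objections stand. They narrow the point without removing it.

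**Conclusion.** The concern holds in this form: two sections of the current text each name a different sole primary outcome, one of them is secondary elsewhere, and neither the sample-size section nor the statistics section says which governs. That conclusion needs no arithmetic.

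The consequence for error control is conditional, and 9.75% is the size of the risk only under the conditions given above. The power shortfall, about 58% against the stated 80%, rests on reading 0.55 as Cohen's d for a two-group comparison with no adjustment for baseline. It is a separate weakness, but it belongs here because choosing either primary outcome would otherwise leave an unsupported power claim in place.

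This must be fixed. It is cheap to do so, since the article describes the trial as still recruiting with no interim analysis planned.

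**What to change.** Before any unblinded look at the data:

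1. Name one primary outcome in identical words in the abstract, Primary outcomes, Sample size estimation and Statistical methods, and make the other secondary. The choice is the sponsor's, as the article contains support for each.
2. Define it as one number per participant with one matching test:
   - If VAS craving is chosen, use (T7−T5)−(T3−T1), compared between groups.
   - If the ventral striatum is chosen, use one ROI-mean food-minus-neutral contrast, post minus pre, compared between groups.
3. Say what role FCQ-T has, and make the group-by-time analysis refer to the chosen endpoint.
4. Restate the power for that endpoint whichever is chosen. Give the type of effect size, the measure it comes from and any pre–post correlation assumed. If no effect size can be justified for the endpoint, state the effect detectable at 32 per arm (d = 0.71 for 80% power with a two-group t-test) and withdraw the claim based on 0.55.
5. Check that the registry entry matches the choice, and update it if it does not.

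The cost is amended wording, a short recalculation and a registry check. No new data are needed.

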**Discussion:**

The results will provide novel insight into neuroscience for the efficacy of tDCS and will advance the field towards precision medicine for obesity. Exploratory results will examine the potential predictive biomarkers for tDCS response and eventually provide personalized intervention for the treatment of obesity.

**Trial registration:**

Iranian Registry of Clinical Trials (IRCT) IRCT20121020011172N4. Retrospectively registered on 4 June 2020

## Background

Given the worldwide increase of the proportion of overweight or obese adults, the development of interventions to modulate food-related brain processes and functions is of great scientific and public interest [1]. There is a large body of existing evidence that studies the correlation of BMI with neural, behavioral, or psychological parameters [2–7]. BMI has been also positively associated with food craving [8–10]. Food craving plays an important role in the etiology of overweight and obesity with increasing total energy intake [11, 12]. Such craving is a form of food cue-reactivity: a conditioned appetitive response to food cue that is mostly accompanied by increased salivation [13] and neural activity in gustatory and reward-relevant brain areas [14]. As such, food craving and other forms of food cue-reactivity may function as conditioned responses that serve as triggers for increased food consumption [15] and weight gain [16], which may exacerbate the risk for rising obesity rates [17]. Albeit there are positive outcomes in controlling obesity using nutritional, psychological, and pharmacological approaches, a majority of patients with frequent food cravings manifest a chronic, relapsing course of disease within 1 year of obesity treatments [18–20] resulting in a need for alternative or adjuvant treatment options. Therefore, non-invasive neuromodulation approaches have been extensively investigated to regulate food craving by modulating the relevant dysregulated networks and neural activity as a possible approach to organize the decision-making process and control the behaviors of food cravers [21–24]. In this context, transcranial direct current stimulation (tDCS) has aroused particular interest in research and practice in recent years.

In order to determine the neurophysiological, cognitive, or clinical effects of non-invasive brain stimulation (NIBS), most studies compare the effects of active stimulation with a sham intervention. Hence, sham tDCS protocols are fundamental because of the placebo response observed in NIBS trials [25] and the fact that nonblinded trials overestimate the effects of subjective and objective results [26].

The therapeutic potential of tDCS intervention for obesity is hypothesized to be based on the modulation of dysregulated top–down control by prefrontal cortex (PFC) function and reward processing in subcortical-limbic structures, mainly the ventral striatum. In recent years, data derived from neuroimaging and cognitive assessments provide evidence that food cue-reactivity, particularly in obese persons, is associated with dysregulated activities within the prefrontal regions, specifically, the dorsolateral prefrontal cortex (DLPFC). The potential for DLPFC neuromodulation might remediate these dysregulated activities within prefrontal brain regions that have been associated with both impaired inhibitory control (i.e., binge eating and purging) and poor cognitive flexibility (e.g., the obsessive concerns with eating, weight, and shape) [12, 22–24].

Accordingly, therapeutic strategies that modulate brain activity in the DLPFC might regulate or suppress food cue-reactivity, cravings, and appetite. Examining the effect of cortical activity modulation using high-frequency rTMS over the left DLPFC in eating disorders and obesity was tested in many studies and a temporary anti-craving effect of this modulation has been demonstrated [27, 28]. Another clinical study also reported beneficial effects of using high-frequency rTMS applied over the left DLPFC to modify cue-induced food cravings and binge eating in people with a bulimic eating disorder [29]. This finding was replicated using bilateral tDCS to the DLPFC (anode over F4/cathode over F3), which demonstrate a reduction in self-reported cravings for active stimulation as compared to sham stimulation [30–32].

However, no study has evaluated the neurofunctional mechanisms of action of tDCS on food cue-reactivity. Therefore, the present study was designed as a randomized parallel-design, sham-controlled, double-blind trial to investigate the neurofunctional mechanisms of action for tDCS to modulate food cue-reactivity and cravings in ones with obesity or overweight problems using fMRI. We focused on the following aims in this trial:
To determine whether tDCS over DLPFC changes subcortical-limbic reactivity to food cues in obesityWhether tDCS could be an effective intervention for reducing food cravingTo determine how tDCS affects neural correspondence of craving using fMRITo determine the efficacy of tDCS on suppression of craving that influenced by individual baseline differencesTo explore which of (a) subjective, (b) clinical, (c) behavioral, (d) structural, or (e) neural circuits measures predict tDCS induced craving reduction in obesity

## Methods/design

### Design and setting

This study is conducted according to a double-blind randomized sham-controlled design, and it is a single-center superiority trial, which was conducted at the National Brain Mapping Lab, Tehran, Iran. The study is currently recruiting and 64 subjects with obesity or overweighed between the age of 18 and 61 years are to be randomly divided into two parallel arms which deliver active or sham DLPFC tDCS. A single-session bilateral tDCS over the DLPFC is applied in half of the subjects while the other half receives sham stimulation.

The course of the trial is visualized in Fig. 1.

**Fig. 1 Fig1:**
[figure not shown]
The NeuroStim-Obesity flowchart

After signing the consent form, eligible participants undergo intensive baseline assessments using self-report and clinical assessments. Participants in the active arm receive 2 mA anodal tDCS for 20 min over the right DLPFC with the cathode over the left DLPFC. The set-up for sham and real stimulation sessions is exactly the same. Structural, resting-state (rs), and task-based functional MRI (pictorial food cue exposure) was done immediately before and after active or sham tDCS. Immediate craving is assessed with a single item 0–100 VAS question at multiple time points before and after imaging and tDCS. The Ethics Committee of Iran University of Medical Sciences approved the research to trial (IR.IUMS.REC.1396.0459), which is registered with the Iranian Registry of Clinical Trials (IRCT20121020011172N4).

